
## 3. Discussion

This protocol is for a randomized, controlled trial primarily investigating the potential enhancement of antidepressant efficacy of MECT for major depressive disorder by AA treatment. Additionally, secondary outcomes in exploratory studies will include evaluating the effects of AA on other variables of MECT and related general anesthesia, and whether AA can prevent worsening of, or even improve, the adverse effects. We will also explore the associated molecular biomarkers potentially underlying these effects. To the best of our understanding, this represents the first randomized controlled trial designed to evaluate the effects of AA treatment on individuals diagnosed with major depressive disorder undergoing MECT, specifically targeting the potential augmentation of AA treatment on MECT efficacy.

This study will reasonably and rigorously provide robust clinical evidence and will adhere to the Consolidated Standards of Reporting Trials (CONSORT) 2025 Statement guidelines [48]. The prospective, randomized, blind, placebo-controlled method, along with a justified sample-size estimation, allows for the potential detection of intergroup differences and the identification of relevant effects through comparative analysis. Patient selection will be restricted to individuals with major depressive disorder who were clinically indicated for MECT. Both the electroconvulsive therapy and anesthesia procedures will be administered according to standard clinical routine protocols, unaffected by trial participation, thereby ensuring balanced implementation across study groups.

The proposed dose of AA has been determined based on the safety range specified in the manufacturer’s prescribing information and previously reported doses in the literature, optimizing therapeutic efficacy and ensuring medication safety [32,49]. The dose of AA was selected based on a comprehensive consideration of clinical evidence, pharmacokinetic principles, and the safety profile. Clinical studies have demonstrated that adjunctive use of AA (500 mg twice daily) significantly improved depressive symptoms and was well-tolerated in both adult and pediatric patients with major depressive disorder [32,50]. Pharmacokinetic studies have indicated that a 500 mg dose maintained plasma AA concentrations above the neuroprotective threshold (>50 μmol/L), while avoiding gastrointestinal adverse effects and absorption saturation associated with single doses exceeding 1000 mg [51]. Furthermore, high-dose intravenous AA (median 22.5 g/d, up to 100 g/d) has not been associated with a higher risk of adverse events than placebo in randomized controlled trials [52], further supporting the rationale and safety of the 500 mg intravenous dose to be used in this study. Nevertheless, all potential adverse events will be closely monitored and systematically documented, with appropriate interventions provided as necessary, thereby ensuring the safety and well-being of participants throughout the study.

Comprehensive monitoring of outcomes captures intervention efficacy from multiple angles: clinical endpoints including depressive symptoms; suicidality; cognitive function; psychotic symptoms; seizure parameters; anesthetic variables; and blood biomarkers. This multidimensional approach is designed to provide both efficacy evidence and possible mechanistic clues [53,54,55,56]. Measurements will be collected by independent investigators who remain blind to both the experimental intervention and group allocation. In addition, all subjective rating scales used are currently recognized and widely used standardized instruments for the relevant measurements. To control the measurement quality and enhance the reliability of the results, assessments will be conducted by psychiatrists who have received strict, study-specific training.

The mechanistic rationale for this study focuses specifically on pathways potentially relevant to AA and MECT synergy. AA may target mechanisms that complement MECT, primarily through its potent antioxidant and anti-inflammatory effects [14,15,16], which could mitigate oxidative stress associated with both major depressive disorder and the MECT procedure itself. Furthermore, AA’s role in modulating BDNF and synaptic plasticity [15,16,17,18] represents another key pathway, as BDNF signaling is implicated in the therapeutic action of MECT. The biomarker analyses in this study will preliminarily explore these specific mechanisms, antioxidant/anti-inflammatory effects and BDNF modulation—to provide clues for future research.

Therefore, we hypothesize that the adjunctive use of the potent antioxidant AA during MECT may directly counteract oxidative stress processes and affect potential downstream targets. By mitigating cumulative oxidative neuronal damage, we propose that AA creates a more favorable condition for the antidepressant effects of MECT, representing a potentially key mechanistic pathway through which AA enhances the therapeutic efficacy of MECT. Although further mechanistic investigation is warranted, this study will provide clinical evidence that may support translational applications.

Some limitations of this study may exist. First, the single-center design may limit generalizability, though standardized protocols maximize internal validity. Second, despite rigorous rater training, a degree of subjectivity inherent to clinician-rated scales remains unavoidable. Third, regarding the electrophysiological monitoring of MECT sessions, the EEG-based evaluation of seizure adequacy relied on traditional observational methods (e.g., visual inspection of seizure duration and morphology). This approach is inherently subjective and lacks the objective, quantitative metrics that modern automated EEG analysis tools could provide, potentially introducing assessment bias. Fourth, the biomarker analyses are exploratory in nature. While they may reveal valuable associations, the correlations observed cannot establish causality between the changes in biomarker levels and the clinical outcomes.

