### 2.2 Participants

Potential participants will be screened at the Department of Psychiatry in the First Affiliated Hospital of Chongqing Medical University. Eligible participants will be enrolled after providing written informed consent and may withdraw from the study at any point.

Inclusion Criteria: (1) Diagnostic and Statistical Manual of Mental Disorders, Fifth Edition (DSM-5) diagnosis of major depressive disorder requiring MECT and hospitalization; (2) aged 18–59 years; (3) body mass index (BMI) between 18.5–30 kg/m^2^; (4) physical status (American Society of Anesthesiologists, ASA) I–II, without major comorbidities; (5) willingness of the patients and/or their legal guardian to offer written informed consent.

Exclusion Criteria: (1) comorbid with severe medical and/or surgical diseases, including significant cardiovascular or cerebrovascular diseases, uncontrolled hypertension, elevated intracranial pressure, or the presence of cardiac pacemakers or intracranial implants; (2) co-occurring psychiatric disorders (e.g., schizophrenia); (3) conditions that may interfere with efficacy assessments (e.g., catatonia (diagnosed by experienced psychiatrists according to DSM-5 criteria), cognitive impairment, illiteracy, or intellectual disability); (4) contraindications to anesthesia or MECT (e.g., full stomach, severe pulmonary dysfunction, known allergy to anesthetics); (5) known allergy to ascorbic acid or any contraindications to its administration; (6) history of alcohol or other substance dependence; (7) previous ineffectiveness or serious adverse effects of MECT; (8) pregnancy; (9) participation in another clinical trial within the past year.

Participants will be discontinued from the study if any of the following occur: (1) serious adverse effect necessitating termination of the intervention; (2) request by the patient and/or family to withdraw; (3) clinical circumstances evaluated by the treating psychiatrist that warrant discontinuation of MECT (e.g., remission according to the 24-item Hamilton Depression Rating Scale (HAMD-24) criteria, defined as a score of <10 on two consecutive assessments, occurrence of severe cognitive impairment, intolerable reactions, or no clinical improvement after eight MECT sessions, etc.); (4) violation of trial protocol.

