### 2.5 MECT Procedure

The MECT protocol is determined by the treating psychiatrist, initiated with up to four weekly sessions during the first treatment week before transitioning to a maintenance schedule of three sessions per week. The procedure utilizes a Thymatron DGx device (Somatics, LLC, Lake Bluff, IL, USA) with bitemporal electrode placement positioned 5 cm superior to the lateral orbital rim. Stimulation parameters consist of square-wave stimulation at 900 mA, with 125 bidirectional pulses per second and a brief-pulse width of 1.5 ms [33]. The initial electrical charge is calculated using the half-age method, with subsequent doses adjusted in 5% increments per session based on continuous electroencephalography (EEG) monitoring of seizure characteristics including morphology and duration. Anesthetic administration includes intravenous atropine (0.5 mg), propofol (2 mg/kg), and succinylcholine (1 mg/kg), with dosage customization according to individual patient response to achieve optimal seizure expression. The electrical stimulus will be delivered immediately following the cessation of succinylcholine-induced fasciculations, under conditions of adequate oxygenation. Treatment efficacy is confirmed through electrographic seizure duration exceeding 25 seconds [34,35] and characteristic EEG patterns demonstrating polyspike-wave complexes, 3-Hz spike-and-wave discharges, and postictal suppression [33,34,36].

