### 2.8 Statistical Analysis

The intention-to-treat (ITT) analysis set in this study will include all randomly assigned participants, regardless of whether they received MECT treatment or completed the follow-up assessments. Analyses will be conducted using SPSS (version 26, IBM Corp., Armonk, NY, USA). Missing outcome or covariate data, including those from participants in the ITT set without post-baseline data, will be handled using multiple imputation, and a mixed model for repeated measures (MMRM) will be used where appropriate. For the primary outcome (the rate of response to MECT), binary logistic regression, with treatment group as the independent variable and pre-specified stratification factors included as covariates, will serve as the primary analytical method, and results will include an adjusted odds ratio (aOR) with a 95% confidence interval. Additionally, potential interaction effects between the stratification factors (age, sex, baseline HAMD-24 score) and the treatment group will be explored within this model for the primary outcome. The Chi-square test will be used as a supplementary analysis. Categorical variables, expressed as counts (percentages), will be compared between groups using the Chi-square test (or the Fisher’s exact test). Continuous variables will be presented as mean (standard deviation) (if normally distributed) or median (interquartile range) (if non-normally distributed), and compared using *t*-test or nonparametric tests (e.g., Mann-Whitney U test), as appropriate. For secondary-outcome analyses, logistic regression will be performed to adjust for potential confounders. For multiple comparisons, the Bonferroni correction will be applied for the secondary and exploratory outcomes. Specifically, the Bonferroni correction will be applied uniformly across all pre-specified secondary outcomes to control the family-wise error rate. We acknowledge that this is a conservative approach, which prioritizes the control of Type I error over statistical power for these outcomes. Given their exploratory feature, between-group differences in blood biomarker levels from baseline to post-treatment will be compared using an analysis of covariance (ANCOVA) adjusted for baseline values, and the Benjamini–Hochberg false discovery rate (FDR) procedure will be applied to correct for multiple testing. Pre-specified subgroup analyses will be conducted based on age (<45 and ≥45 years), sex (male and female), and baseline HAMD-24 score (divided at the median). These analyses will be performed by including an interaction term between the treatment group and the subgroup variable in the primary statistical model (binary logistic regression). Given the exploratory and hypothesis-generating nature of these subgroup analyses, no multiplicity adjustment will be applied to the interaction tests, and the results will be interpreted with caution. Sensitivity analyses will include the per-protocol (PP) analysis and complete-case analysis, an evaluation using alternative missing-data-handling strategies, and re-analyses excluding specific populations (e.g., protocol violators) to assess the robustness of the findings. All hypothesis tests will be two-tailed, and a statistical significance level will be set at* p *< 0.05.

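### The per-patient adverse-effect comparison estimates AA's total effect but cannot show direct protection, because the number of MECT sessions depends on outcome

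*Protocol article*

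**What the plan says.** **Course length.** Section 2.5 states that "The MECT protocol is determined by the treating psychiatrist" and gives a weekly frequency but no fixed number of sessions. Charge is adjusted from session to session on the EEG, and anaesthetic doses on individual response. Section 2.2 discontinues participants for "clinical circumstances evaluated by the treating psychiatrist that warrant discontinuation of MECT". Its examples are "remission according to the 24-item Hamilton Depression Rating Scale (HAMD-24) criteria, defined as a score of <10 on two consecutive assessments", severe cognitive impairment, intolerable reactions, and no improvement after eight sessions.

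**Collection.** Table 1 schedules adverse effects of AA and of MECT at each MECT session and before discharge.

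**Analysis.** Section 2.8 gives no method specific to adverse effects. The general rule is "Categorical variables, expressed as counts (percentages), will be compared between groups using the Chi-square test" or Fisher's exact test. It adds: "For secondary-outcome analyses, logistic regression will be performed to adjust for potential confounders". The confounders are not named, and Table 1 lists safety outcomes apart from secondary outcomes.

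**Aim.** Section 2.1 includes the tolerability of MECT in the objective. The Introduction hypothesises, cautiously, that AA might alleviate MECT adverse effects directly. The Discussion plans to evaluate "whether AA can prevent worsening of, or even improve, the adverse effects".

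**Balance.** The Discussion describes electroconvulsive and anaesthetic procedures as following clinical routine, "unaffected by trial participation, thereby ensuring balanced implementation across study groups".

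**The concern.** Applying one set of rules to both arms does not make the delivered treatment equal when the rules respond to outcome. If AA changes how soon patients remit, how well they tolerate treatment, or how often they fail to improve, the arms will differ in sessions, anaesthetics, infusions and delivered charge. They will also differ in the number of occasions on which adverse effects are sought. The Discussion itself plans to examine what AA does to MECT and anaesthesia variables, so these cannot at the same time be taken as balanced.

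At stake is the reading of a named aim. A lower percentage of AA patients with an adverse effect could come from a lower risk at each session, from fewer sessions, or from both. A higher percentage could likewise come from a longer course. The stated comparison does not separate these, and nothing stated in sections 2.6 to 2.8 would show the reader the number of sessions by arm.

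**Working it through.** **1. The plan's own figure.** The protocol gives no session counts or adverse-effect rates. Its one relevant calculation is the sample size in section 2.7 (60% vs 80%, two-sided α 0.05, power 85%, 1:1). With the pooled-variance formula:

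n = [1.960·√(2·0.7·0.3) + 1.036·√(0.6·0.4 + 0.8·0.2)]² / 0.2² = (1.270 + 0.655)² / 0.04 ≈ 92.7, so 93 per group.

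93 / (1 − 0.225) = 120 per group. Both figures reproduce and are not in dispute.

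**2. Set-up of the illustration.** All of the following are assumptions except the 120 per arm and the 80% and 60%:
- the per-session risk q is the same in both arms (AA has no per-session effect), from 2% to 20%;
- sessions are independent;
- P(at least one event in k sessions) = 1 − (1 − q)^k.

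The chance of significance uses the normal approximation for two proportions with 120 per arm and counts only results in the stated direction. With no difference between arms it would be 2.5%.

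**3. Scenario tied to 80% vs 60%.** The pilot response rates stand in for the share stopping early. Early stoppers receive 6 sessions and the others 12. Mean sessions are 0.8·6 + 0.2·12 = 7.2 (AA) and 0.6·6 + 0.4·12 = 8.4 (placebo). For q = 5%, the risk is 26.5% over 6 sessions and 46.0% over 12, so:
- AA: 0.8·26.5 + 0.2·46.0 = 30.4%
- Placebo: 0.6·26.5 + 0.4·46.0 = 34.3%

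| q | AA | Placebo | Difference (points) | Chance of p<0.05 favouring AA |
|---|---|---|---|---|
| 2% | 13.4% | 15.5% | 2.0 | 7% |
| 5% | 30.4% | 34.3% | 3.9 | 9% |
| 10% | 51.8% | 56.8% | 5.0 | 12% |
| 20% | 77.7% | 81.5% | 3.9 | 11% |

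**4. Other assumed session gaps.** Here every patient in an arm has the same number of sessions.

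| Sessions, AA vs placebo | Difference over q = 2% to 20% (points) | Chance of p<0.05 favouring AA |
|---|---|---|
| 8 vs 9 | 1.7 to 4.3 | 6% to 11% |
| 8 vs 10 | 3.4 to 8.2 | 10% to 27% |
| 6 vs 8 | 3.5 to 10.1 | 12% to 43% |
| 6 vs 10 | 6.9 to 18.3 | 32% to 88% |

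**5. Reversed direction.** If improvers (80% vs 60%) continue to 10 or 12 sessions and the others stop at 8, AA appears worse by 0.7 to 3.0 points.

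In every scenario the per-session risk is q in both arms, so the differences come from session numbers alone.

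**The case against.** - **The percentage is a legitimate estimate.** If AA shortens the course and fewer patients then have side effects, assignment to AA caused that benefit, and it answers the tolerability question in section 2.1. This stands. Only attributing the difference to a direct effect lacks support, and the protocol words that hypothesis cautiously.
- **No method specific to adverse effects is stated.** The rule cited is the general one for categorical data, and an analysis plan not shown may say more. This stands in part. The point therefore rests on the balance assurance, which is in the text, and on what the stated method can support. Missing detail is not the complaint.
- **The Discussion sentence may mean only that the same procedures apply in both arms.** That reading is defensible, and it is what the sentence should say. As written, it infers balanced implementation from routine care.
- **Large effects need large assumed gaps.** This stands. The scenario tied to the protocol's own rates gives modest differences. Positive within-patient correlation would generally shrink them, and a Bonferroni correction, if it covered these outcomes, would lower the chance of significance.
- **Cognition is scored by MoCA at baseline and before discharge.** The argument about per-patient percentages and repeated occasions does not apply to that score.
- **Per-session rates have their own bias.** Later sessions come from patients selected by outcome, so such a contrast must not override the randomised one. This stands and shapes the fix.

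A reader might infer that treatment ends on response and that the comparison is bound to flatter AA. The documents do not support this. Response is a reduction of at least 50% measured at the end of treatment (section 2.6). The listed stop is remission, one example among several, and the others can shorten the course of patients who do poorly.

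**Conclusion.** The point holds in a limited form. The assurance of balanced implementation does not follow from sections 2.2 and 2.5. The stated comparison of adverse effects estimates the total effect of assignment to AA and cannot, by itself, support a claim of direct alleviation.

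Under equal per-session risk, the scenario tied to 80% vs 60% gives about 2 to 5 points, with a 7% to 12% chance of a significant result favouring AA. Assumed gaps up to 6 vs 10 sessions give up to about 18 points, and the sign can reverse. All of this depends on assumed session counts, risks and independence between sessions. The likely harm is misinterpretation of a difference and not a near-certain false positive. The change is worth making because it affects what can be concluded about a named aim. It concerns safety conclusions only.

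**What to change.** 1. **Discussion:** reword the sentence to claim only that the same procedures and rules apply in both arms, and not that the delivered treatment is balanced.
2. **Section 2.6:** report the number of MECT sessions and the delivered charge by arm.
3. **Section 2.8:** keep the per-patient percentage and label it the total effect of assignment to AA. Add as supplementary analyses (a) adverse effects per session, by a count model with log sessions as offset or by GEE on session-level data, and (b) a comparison over an early fixed set of sessions, chosen before unblinding so that few patients have yet stopped.
4. **Interpretation:** read any claim of direct mitigation in the light of these results.

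The cost is wording and analysis time. Table 1 already records adverse effects and electroconvulsive parameters at each session, so no new visits are needed and no treatment rule changes. The limits should be stated: per-session rates condition on a post-randomisation quantity, and the early-session comparison misses cumulative effects. Both support the randomised per-patient comparison and do not replace or override it.

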## 4. Summary

This proposal is for a double-blind, randomized controlled trial to assess the efficacy, safety, and potential correlated biomarkers of AA as an augmentation strategy for MECT among individuals diagnosed with major depressive disorder. This study is expected to provide an evidence-based, safe, and cost-effective strategy for optimizing MECT protocols, and also offer potential directions for future mechanistic investigations.

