**Methods and Analysis::**

This is a prospective, randomized, double-blind, placebo-controlled trial. We will enroll 240 patients with major depressive disorder scheduled for MECT. Participants will be treated either with intravenous AA (500 mg, n = 120) or with intravenous normal saline (n = 120), administered immediately before each MECT session, just prior to induction of general anesthesia. The primary outcome is the treatment response rate, defined as the proportion of patients with a ≥50% reduction in the 24-item Hamilton Depression Rating Scale (HAMD-24) score. Secondary outcomes include remission rate, presence of psychotic symptoms, cognition, and adverse effects. This study is expected to provide an evidence based, safe, and cost effective strategy for optimizing MECT protocols, as well as potential directions for future mechanistic investigations.

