## 2. Materials and Methods

### 2.1 Study Design and Ethics

This study is a prospective, randomized, double-blind, placebo-controlled, parallel-group clinical trial designed to assess the effect of AA treatment on the therapeutic outcomes and tolerability of MECT in patients with major depressive disorder. The protocol was drafted according to the Standard Protocol Items: Recommendations for Interventional Trials (SPIRIT), and was registered at the Chinese Clinical Trial Registry (Registration No. ChiCTR2500095678) on January 10, 2025. Fig. 1 illustrates the participant flow throughout the study.

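### A safe strategy is anticipated, but adverse effects get only significance testing with no stated interval in a trial sized on response, so a non-significant comparison cannot support the word

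*Protocol article*

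**What the plan says.** Section 2.1 describes the trial as "designed to assess the effect of AA treatment on the therapeutic outcomes and tolerability of MECT". Section 4 gives its purpose as "to assess the efficacy, safety, and potential correlated biomarkers of AA as an augmentation strategy for MECT". Two places then anticipate the result: the Abstract ("This study is expected to provide an evidence based, safe, and cost effective strategy") and section 4 ("This study is expected to provide an evidence-based, safe, and cost-effective strategy for optimizing MECT protocols"). Neither attaches a criterion to the word safe.

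Section 2.8 has no passage specific to adverse effects. Its general rule is "Categorical variables, expressed as counts (percentages), will be compared between groups using the Chi-square test", with Fisher's exact test as the alternative. It closes with "All hypothesis tests will be two-tailed, and a statistical significance level will be set at" p < 0.05. A 95% confidence interval is promised only for the adjusted odds ratio of the primary outcome.

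The status of adverse effects is unclear. The Abstract lists them among the secondary outcomes, while Table 1 places them under a separate safety heading. If they are secondary, two more statements in section 2.8 apply: "For secondary-outcome analyses, logistic regression will be performed to adjust for potential confounders", and a Bonferroni correction across all pre-specified secondary outcomes.

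Section 2.7 bases the sample size on response (60% versus 80%). No power or precision is stated for any harm. Section 2.6 names memory deficits and muscle pain as MECT effects but gives no expected rates.

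**The concern.** A superiority test on adverse effects can flag harm, but it cannot show that harm is absent. If the result is not significant, the reader needs to know how large an excess under AA the data still allow. A count, a percentage and a p-value do not state that directly, and the plan promises no interval for these outcomes.

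This matters because the article already anticipates a safe strategy. In a sample sized for a 20-point difference in response, a smaller but clinically relevant excess of an adverse effect could easily give a non-significant result. The eventual report could then describe AA as safe with MECT while its own data did not exclude such an excess.

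**Working it through.** **Inputs from the article.** 120 enrolled and 93 evaluable per group, 1:1 allocation, two-sided alpha 0.05, and response rates of 60% and 80% with 85% power (section 2.7).

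**Inputs assumed.** Placebo-arm adverse-effect rates of 5%, 10% and 20%. The article gives none, so a range is shown.

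**Step 1: reproduce the plan's own figure.** With p̄ the mean of the two rates and q = 1 − p:

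n = [1.96·√(2p̄q̄) + 1.036·√(p₁q₁ + p₂q₂)]² / (p₂ − p₁)²

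For 0.60 and 0.80, p̄ = 0.70, so n = [1.96·√0.42 + 1.036·√0.40]² / 0.04 ≈ 92.7, or 93 per group. Allowing for 22.5% attrition, 93/0.775 = 120. Both stated figures reproduce.

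**Step 2: power to detect an excess of an adverse effect.** The same test gives

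power = Φ{[d·√n − 1.96·√(2p̄q̄)] / √(p₁q₁ + p₂q₂)}, with d = p₂ − p₁.

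- 5% versus 10%, n = 120: [0.548 − 0.730]/0.371 = −0.49, power 31%.
- 10% versus 20%, n = 120: [1.095 − 0.990]/0.500 = 0.21, power 58%.

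Exact enumeration of the binomial outcomes gives 32.5% and 59.3%, so the approximation is adequate. The chance of missing the excess (1 − power), from exact enumeration at unadjusted 0.05, is:

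| Placebo vs AA (assumed) | Chi-square, 120 | Chi-square, 93 | Fisher, 120 | Fisher, 93 |
|---|---|---|---|---|
| 5% vs 10% | 68% | 75% | 78% | 83% |
| 10% vs 20% | 41% | 52% | 48% | 59% |
| 20% vs 30% | 57% | 65% | 62% | 71% |
| 20% vs 40% | 7% | 14% | 9% | 19% |

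The last row is the mirror image of the design contrast: 20% versus 40% with an event is 80% versus 60% without. It shows the size of harm this sample is suited to detect, namely about 20 points.

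**Step 3: where a doubling is missed more often than not.** Setting power for p versus 2p to 50% gives a placebo rate of about 8.4% at 120 per group and 10.4% at 93. Below these rates a doubling is more likely missed than found; above them the reverse holds.

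**Step 4: what an interval would show.** With equal observed rates p in both groups, the half-width for the risk difference is 1.96·√(2p(1 − p)/n). At n = 120:

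- p = 5%: 1.96·√(0.095/120) = 5.5 points
- p = 10%: 1.96·√(0.18/120) = 7.6 points
- p = 20%: 1.96·√(0.32/120) = 10.1 points

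The matching upper limits for the risk ratio, exp{1.96·√(2(1 − p)/(np))}, are 3.01, 2.14 and 1.66. Equal observed rates would therefore still allow a doubling at 5% and 10%, but would exclude it at 20%.

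**Step 5: if Bonferroni applies.** With an assumed eight secondary outcomes (alpha 0.05/8 = 0.00625), a 10% versus 20% excess is missed about 72% of the time at 120 per group, and 20% versus 40% about 25%. The figures in the table are thus the milder case.

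**The case against.** Several stronger readings are tempting, and the article does not support them.

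- A reader might infer a rule that a non-significant test means safe. No section says this. The sentences in the Abstract and Summary are general expectations, and the Discussion rests the safety of the dose on the prescribing information and earlier studies.
- A reader might infer that the Chi-square or Fisher test is the only comparison available. If adverse effects are secondary, logistic regression is planned too and can yield an odds ratio with an interval, although section 2.8 does not promise one.
- A reader might infer that a doubling of a common adverse effect would usually be missed. That depends on the unstated base rate. It holds below roughly 8% (120 per group) or 10% (93 per group). At 20% versus 40% the excess is found 86–93% of the time.
- A reader might ask for a formal harm margin. In a trial sized for efficacy that is a preference, and its absence is not an error.

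It can also be said that adverse-event summaries are usually specified in a full protocol or analysis plan, neither of which is shown. Cognition, a recognised MECT harm, is also measured by MoCA, where a 0.5-SD difference would be detected with 92–97% power at unadjusted 0.05.

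These points narrow the concern to categorical adverse effects and to excesses smaller than about 20 points. They do not remove it. The printed article sets a stated testing rule beside an anticipated conclusion that the rule cannot support. The wording can be corrected whatever a fuller document contains.

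**Conclusion.** The concern holds in limited form. The article anticipates a safe strategy and names safety and tolerability as aims, but it states no measure of adverse-effect excess with an interval and was sized on response alone. A non-significant adverse-effect comparison in this trial would not be evidence of safety: excesses of 5 to 10 points are missed between about 41% and 75% of the time by the Chi-square test, depending on the assumed placebo rate and on whether 120 or 93 per group are analysed. Excesses of about 20 points from a 20% base would usually be seen.

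These figures rest on assumed placebo rates and on unadjusted two-sided 0.05. Fisher's test, or Bonferroni if adverse effects are treated as secondary, would raise the chance of a miss. The efficacy analysis is not affected.

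**What to change.** In section 2.8, report any adverse event, any serious adverse event and each named MECT effect (memory deficits, muscle pain) as a risk difference, AA minus placebo, with a 95% confidence interval, using a score or exact method where events are rare. Apply no multiplicity adjustment to these comparisons; this also settles the differing status of adverse effects in the Abstract and Table 1 for this purpose. State that a non-significant test is not evidence of safety, and limit any safety statement to the excess that the interval excludes. No harm margin is needed.

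In the Abstract and section 4, say that the trial will estimate the safety of AA with MECT.

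The change affects analysis and wording only, with no new patients or data. The cost is a more guarded safety statement: with 120 per group and equal observed rates of 5% to 20%, the interval will be about ±5.5 to ±10 points.
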